### Randomization

By 1:1 randomization, patients were allocated either to receive the standard single-dose regimen or to be treated according to a novel influenza vaccination schedule comprising the administration of a booster dose 5 weeks after the first vaccination dose. In order to avoid bias due to differences in immunosuppression level of patients between treatment arms, randomization was stratified according to study sites (because local immunization protocols may differ for SOT recipients), type of organ and time since transplantation. Randomization was centralized and computer-generated, with allocation concealed by integrating a locked list into an electronic case report form (eCRF). A copy of the randomization list is guarded in an opaque, sealed envelope by the trial’s Central Management Team (CMT)at the coordination center that is independent from the investigators who recruited patients.

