### Sample size calculation

Sample size was calculated using the results of a Spanish multicenter study in which SOT recipients received a single dose of seasonal influenza vaccination during the 2010–2011 season
[27]. In that study, seroconversion rates against influenza A(H1N1) 2009, influenza A(H3N2) and influenza B were 77%, 67% and 67%, respectively. According to these estimates, we calculated our sample size according to the following criteria:

To achieve a 95% confidence level (significance level of 5%) and 80% statistical power to observe differences in testing the null hypothesis (H0)p1 = p2 using a χ^2^ bilateral test in two independent samples.To obtain an increase in the primary endpoint of 10% (increased percentage of seroconversion rate in the experimental arm), which is considered clinically relevant in the literature. According to this criterion, we would expect to achieve 77% and 87% seroconversion rates in the control and experimental arms, respectively.To estimate a 10% dropout rate per arm.

According to these premises, and using a 1:1 ratio of experimental units to controls, the minimum number of patients was set at 231 units in each treatment arm, with a total of 462 evaluable participants to be recruited for the study. Taking into account the estimated loss percentage, the total number of patients needed for the study was set at 514 (257 participants per treatment arm). Sample size was calculated using the online Simple Interactive Statistical Analysis calculator
[29].

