Efficacy analysis will be performed using seroconversion and seroprotection rates, GMT, GMR and incidence of confirmed influenza infection (to assess clinical effectiveness). The analysis will include, as covariates, previous influenza vaccination, previous record of confirmed influenza infection and other demographic and clinical variables. Additionally, a subgroup analysis will be performed to evaluate effectiveness in patients with decreased response to influenza vaccination (liver failure, use of mammalian target of rapamycin inhibitors, first 6 months posttransplantation).

Vaccination safety analysis will be performed using tabulations of AEs, and descriptive analysis will be provided at baseline and follow-up visits for each treatment group. A tabulation of SAEs will also be provided for each patient within each treatment group. The statistical analysis will be performed by treatment phase (up to 30 days after vaccination) and for the posttreatment phase (long-term follow-up), as appropriate. AEs will be classified on the basis of Medical Dictionary for Regulatory Activities (MedDRA) terminology and summarized for each treatment arm. AE incidence rates will be summarized by system organ class, preferred term, severity and relationship to the IMP. The proportion of patients in each treatment group reporting AEs that occur in ≥3% in each treatment group will be compared using Bayesian methods. The specific system organ classes and preferred terms analyzed will be those reported by at least 5% of the patients in each treatment group.

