A bivariate analysis will be performed to compare primary efficacy outcome, secondary efficacy and safety endpoints between treatment arms of the study. A bivariate analysis using a χ^2^ test or Fisher’s exact test will be used for categorical variables, and the Bonferroni correction will be applied when appropriate. For quantitative variables, the Mann–Whitney *U* test or Student’s t-test based on their distribution will be used. If the variances are not homogeneous (Levene test), the Welch test will be applied (analysis of variance). The relative risks and 95% confidence intervals (95% CI) will be calculated by taking the exponent of the natural logarithm of the mean and 95% CI. Also, the linear trend analysis will be used for multiple comparisons. A multivariate model will be used to adjust for possible confounding variables. The threshold of statistical significance will be set at *P* < 0.05. All reported *P*-values will be based on two-tailed tests. We have optimized the design and conduct of the trial to minimize the number of dropouts and missing data. The analysis will be performed on the ITT population, and missing data will be handled by imputing missingness to failure.

All calculations will be performed using SPSS version 18.0 software (SPSS, Chicago, IL, USA). The TRANSGRIPE1-2 clinical trial has not been programmed with any interim analysis or stopping rules, although the incidence of SAEs is being monitored closely to detect a higher frequency of their occurrence, which may require an early termination of the trial.

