## Discussion

Despite annual vaccination protocols, influenza-associated complications continue to be an important cause of hospitalization and death in SOT recipients
[3, 4]. Although influenza vaccination has proven to be the most effective measure to reduce influenza infection after transplantation
[10], SOT recipients are still vulnerable to influenza infections because their immunological response to vaccination is lower than that of the general population. Thus, efforts are needed to improve influenza vaccine immunogenicity, especially in this vulnerable population with immunosuppression.

Previous researchers have reported a booster effect of seasonal influenza vaccine in patients who have baseline antibody titers
[15, 20]. In a prospective multicenter study, investigators observed that patients with baseline titers had significantly higher sero conversion rates than patients with no baseline antibody titers (90.9% versus 73.0% respectively, for the 2009H1N1 strain and 92.2% versus 62.2%, respectively, for the H3N2 strain). Moreover, patients without preexisting seroprotection at baseline had lower antibody titers after influenza vaccination, whereas patients with baseline antibody titers reached higher GMTs after vaccination
[27]. The hypothesis of the present trial is based on these premises, and we aimed to evaluate the safety and efficacy of a second, booster dose of influenza vaccine administered 5 weeks after the standard seasonal influenza vaccination in SOT recipients.

Preliminary results based on evaluation of the efficacy of a booster dose of influenza vaccination in SOT recipients are controversial. Soesman *et al*.
[17] observed an increased serological rate in liver transplant recipients after the second dose of influenza vaccine (80% double-dose versus 67% single-dose), whereas other studies have shown improved efficacy only after a third dose
[18]. Conversely, other authors have found no benefits of administering a second vaccine dose
[15, 31]. Nevertheless, available evidence is scarce, primarily owing to small sample sizes of the studies, high baseline seroprotection rates, lack of randomization and conditions that are not applicable to the present clinical context, such as different immunosuppression schemes or different circulating virus serotypes
[20, 31].

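### Randomisation is stratified, but the only test named for the primary outcome ignores the strata and the measured baseline titre, and the article does not say whether the unadjusted or the adjusted result is primary: a small, avoidable loss of precision

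*Protocol article*

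**What the plan says.** - **Protocol article, Randomization:** "randomization was stratified according to study sites (because local immunization protocols may differ for SOT recipients), type of organ and time since transplantation". The stated purpose is to avoid imbalance in immunosuppression between the arms, so the authors regard these factors as prognostic.
- **Protocol article, Statistical analysis:** "A bivariate analysis will be performed to compare primary efficacy outcome, secondary efficacy and safety endpoints between treatment arms of the study". For categorical variables the test is chi-square or Fisher's exact. For quantitative variables it is Mann–Whitney, Student's t or Welch, chosen on distribution and on a Levene test. None of these uses the strata.
- **Protocol article, Sample size calculation:** the trial is sized for "80% statistical power to observe differences in testing the null hypothesis (H0)p1 = p2 using a χ^2^ bilateral test in two independent samples", which is the same unstratified comparison.
- **Protocol article, Statistical analysis, on adjustment:** "The analysis will include, as covariates, previous influenza vaccination, previous record of confirmed influenza infection and other demographic and clinical variables". A later sentence adds a multivariate model, whose purpose is to deal with possible confounders.
- **Protocol article, Selection and enrollment:** blood is drawn before the first dose to quantify the baseline humoral response, so a baseline titre is planned for every patient.
- **Protocol article, Discussion:** "patients with baseline titers had significantly higher sero conversion rates than patients with no baseline antibody titers (90.9% versus 73.0% respectively" for 2009 H1N1). For H3N2 the contrast is 92.2% v 62.2%.

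The article does not say whether the bivariate test or the adjusted model is the primary analysis.

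**The concern.** When arms are balanced within prognostic strata, a test that ignores the strata uses a standard error that is too large. Its p-values are slightly too high and its intervals slightly too wide. Baseline titre is a separate matter. It is not balanced by design, so ignoring it leaves the test at its correct size but gives up precision.

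The planned adjustment does not clearly recover this. Confounder control is not the reason to adjust a randomised comparison, and an open-ended covariate list leaves the choice of variables for later. The two covariates that are named, prior vaccination and prior confirmed infection, are indirect markers of something the trial measures directly. With two analyses of the same endpoint and no stated order, there is also discretion over which one counts. At stake are some power and the clarity of the primary result, not its validity.

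**Working it through.** **1. The plan's own sample size.** Inputs from Sample size calculation: two-sided 5%, 80% power, and "we would expect to achieve 77% and 87% seroconversion rates in the control and experimental arms, respectively".

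n per arm = [1.960 × √(2 × 0.82 × 0.18) + 0.842 × √(0.77 × 0.23 + 0.87 × 0.13)]² / 0.10² = (1.065 + 0.453)² / 0.01 ≈ 230.5, so 231.

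231 / 0.9 = 256.7, so 257 per arm and 514 in total. Both figures reproduce exactly. With a continuity correction n would be 251, so the plan assumes an uncorrected, unstratified chi-square. Power at 231 per arm is 80.1%.

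**2. Share of patients with a baseline titre (derived, not stated).** The source study gives "seroconversion rates against influenza A(H1N1) 2009, influenza A(H3N2) and influenza B were 77%, 67% and 67%, respectively" overall. The Discussion gives the rates by baseline titre from the same cited study. Solve for the share q:
- H1N1: 0.730 + 0.179q = 0.77, so q = 0.223.
- H3N2: 0.622 + 0.300q = 0.67, so q = 0.160.
- Influenza B: no rates by baseline titre are given.

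**3. Outcome variance explained by titre present or absent.** R² = q(1 − q)(difference)² / [p(1 − p)]:
- H1N1: 0.1735 × 0.0320 / 0.1771 = 3.1%.
- H3N2: 0.1344 × 0.0900 / 0.2211 = 5.5%.

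**4. What adjustment buys.** The standard error falls by 1 − √(1 − R²), and the effective n is 231 / (1 − R²).

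| Contrast | R² | SE falls by | Worth per arm | Power, 77% v 87% |
|---|---|---|---|---|
| H1N1 | 3.1% | 1.6% | about 7 patients | 80.1% to 81.3% |
| H3N2 | 5.5% | 2.8% | about 13 patients | 80.1% to 82.3% |

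A simulation of 100,000 trials compared the chi-square with a Mantel–Haenszel test stratified on titre. Power rose from 80.5% to 81.4% at the H1N1 rates, and from 67.1% to 68.9% at the H3N2 rates (67% v 77%). Under no effect the chi-square rejected in 4.9% and 5.1% of trials, so ignoring titre does not disturb its size.

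**5. At actual enrolment.** 499 × 0.9 ≈ 449 evaluable. Unadjusted power for 77% v 87% is 78.9%, and 80.2% at the H1N1 R². For 67% v 77% it rises from 65.6% to 68.1% at the H3N2 R².

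**6. If the share with a titre differs from step 2.** For q from 10% to 70%, adjusted power at 231 per arm is 80.7% to 82.3% with the H1N1 contrast and 81.5% to 85.5% with the H3N2 contrast.

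**7. The stratification factors.** The article gives no outcome rates by site, organ or time, so R² must be assumed. If arms are balanced within strata, the true size of the unstratified 5% test is 2[1 − Φ(1.96 / √(1 − R²))].

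| Assumed R² | True size of 5% test | Power if stratified |
|---|---|---|
| 2% | 4.8% | 80.9% |
| 5% | 4.4% | 82.1% |
| 10% | 3.9% | 84.1% |

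**The case against.** **Adjustment is already planned.** The covariate sentence applies to seroconversion, seroprotection, GMT and GMR, and a multivariate model follows. Organ and transplant date are listed in Table 3 and could fall within the open-ended remainder. This stands: the loss is certain only for the bivariate comparison. A reader might infer that the plan makes no adjustment at all, or that GMT and GMR are compared with no regard to baseline. The text does not support either reading. What remains is that the one test tied by name to the primary outcome, and used to size the trial, is unstratified, and that its standing relative to the adjusted model is left open.

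**The covariate list belongs in the analysis plan.** That is fair for the list itself, and its absence from a condensed article is no fault. The point is about the method the article does state.

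**Seroconversion and GMR already use baseline.** Both are defined relative to it. But the Discussion shows that seroconversion still depends strongly on baseline titre, so the definition does not remove its prognostic value.

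**The loss is small.** This stands. A reader might set the H1N1 gain against the 15 patients by which enrolment fell short (514 − 499) and conclude that it more than makes up for them. That works only if all 499 are evaluable: 499 × [1/(1 − 0.0314) − 1] = 16. With the planned 10% loss it is 449 × 0.0324 ≈ 15. If 10% are missing and counted as failures, as the plan provides, R² falls to 2.1%, worth about 11 patients.

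**Conclusion.** The point holds as a minor matter of efficiency and clarity. The named primary comparison does not follow the stratified design and does not use the measured baseline titre. The planned adjustment is framed as confounder control, without naming either, and without a stated rank.

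The size on the documents' figures is about 1 power point at the H1N1 contrast, which is the basis of the sample size, and about 2 to 2.5 at the H3N2 contrast. This rests on the overall and by-titre rates describing the same patients, and on similar shares with a baseline titre in this trial. Titre is treated as present or absent; a continuous log titre might add more, but the documents do not show how much.

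The gain from the strata and the 4.8% to 3.9% range for the true test size rest on an assumed R² of 2% to 10%. A reader might infer a threat to validity. There is none: the test does not inflate false positives, and any error from ignoring the strata is on the conservative side.

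**What to change.** Name one primary analysis of seroconversion for each strain: a pre-specified logistic model with arm, log baseline titre for that strain, organ, time-since-transplant stratum and centre. Report it as a standardised risk difference and risk ratio, so that the effect stays on the scale used for sizing. Enter centre as a random effect or pool small centres. Twelve sites by four organs already give 48 cells, about 10 patients each at 499, and even two time strata (the number is not stated) would halve that to about 5. Keep the chi-square as a sensitivity analysis.

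Compare post-vaccination log titres by ANCOVA with baseline log titre and the same factors, which gives one arm contrast for both GMT and GMR. If the correlation of log titres with baseline is 0.3 to 0.6 (an assumption), this cuts variance by r², that is 9% to 36%, against an unadjusted comparison of post-vaccination titres.

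The cost is wording in the analysis plan, settled while the analysts are still blinded. The variables are already collected, and no patient, visit or assay is added.

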### Outcome measures

Seroconversion rate was the primary end-point variable of the study. Microneutralization assays were performed to quantify neutralizing antibody titers against the two influenza A strains and the influenza B strain. Immunological response and vaccination efficacy were based on the following international criteria: (1) geometric mean titers (GMT; mean antibody titer in the group of vaccinated individuals), (2) seroprotection rate (percentage of patients with antibody titers ≥1:40), (3) seroconversion rate (percentage of participants with four fold increase in antibody titers from baseline) and (4) geometric mean ratio (GMR; seroconversion factor postvaccination compared with prevaccination). Neutralizing antibody titers were evaluated at 5, 10 and 15 weeks and 1 year after influenza vaccination. Cellular immune response to vaccination was determined by quantifying influenza-specific CD4+ and CD8+ memory cells at baseline, 15 weeks and 1 year after influenza vaccination. For each treatment arm, clinical efficacy was assessed by evaluating the episodes of confirmed influenza infection during a 1-year follow-up period. The safety endpoints at each evaluation time frame were rejection episodes, hospitalization, graft loss, mortality, incidence of AEs and severe AEs and rates of discontinuation due to AEs.

In order to study in-depth the immune response to influenza vaccination in SOT recipients, we will also explore other genetic and biological outcomes in the collected samples. Genetic expression patterns of immune response and anti–human leukocyte antigen levels induced by influenza vaccination will be analyzed as ancillary outcomes.

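### Wherever the plan's Bonferroni correction is used, Holm's step-down keeps the same 5% familywise error and rejects at least as often: a cheap efficiency gain, not an error in the plan

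*Protocol article*

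**What the plan says.** Under Outcome measures, the protocol article makes the seroconversion rate the primary endpoint and measures it by strain: "Microneutralization assays were performed to quantify neutralizing antibody titers against the two influenza A strains and the influenza B strain". It gives no rule on whether success means one particular strain, any strain or all strains.

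Under Statistical analysis, treatment arms are compared on primary, secondary and safety endpoints together. Categorical variables get a chi-square or Fisher's exact test, "and the Bonferroni correction will be applied when appropriate". Quantitative variables get a t-test, Welch or Mann-Whitney test with no correction attached. The same paragraph mentions a linear trend analysis for multiple comparisons, which is not a familywise-error procedure. It also sets the threshold at a two-tailed 5% and plans relative risks with ordinary 95% confidence intervals. Bonferroni is therefore the only familywise-error procedure named, and the family it covers is not defined.

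Under Sample size calculation, the earlier single-dose study supplies control rates by strain: "seroconversion rates against influenza A(H1N1) 2009, influenza A(H3N2) and influenza B were 77%, 67% and 67%, respectively". The trial is sized on one comparison, the H1N1 rate: "we would expect to achieve 77% and 87% seroconversion rates in the control and experimental arms, respectively". The criteria are stated as "To achieve a 95% confidence level (significance level of 5%) and 80% statistical power", with no division of the 5%.

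**The concern.** Single-step Bonferroni compares every P-value in a family of three with 0.05/3. Holm orders the P-values and compares the smallest with 0.05/3, the next with 0.05/2 and the largest with 0.05, stopping at the first failure. The first step is the same, so Holm can never reject less. Its control of the familywise error needs no assumption about dependence.

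The two differ most when several hypotheses in the family are false. A trivalent booster that works could plausibly raise the response to all three strains, which is that situation. The sample size was set at an unadjusted 5%, so any correction across strains costs power that was not budgeted. A procedure that recovers part of that power without weakening error control is worth having. What is at stake is how many strains the trial can report as improved, not whether its error control is sound.

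**Working it through.** **Inputs from the article.** Control rates 77% (H1N1), 67% (H3N2) and 67% (B); 10-point increase, stated for 77% to 87%; 231 evaluable per arm; 1:1 allocation; two-sided 5%; 10% dropout.

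**Assumptions not in the article.** The 10-point increase also holds for H3N2 and B (67% to 77%); the correlation between strains, taken over a range; the correction is applied across the three strains.

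**Step 1: reproduce the sample size.** n = [1.960·√(2·0.82·0.18) + 0.8416·√(0.77·0.23 + 0.87·0.13)]² / 0.10² = (1.0649 + 0.4534)² / 0.01 = 230.5, so 231 per arm. Then 231/0.9 = 256.7, so 257. Both match the article at an unadjusted 5%.

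**Step 2: per-strain power at 231 per arm.** Power = Φ[(0.10 − z·√(2p̄q̄/n)) / √((p₁q₁ + p₂q₂)/n)].

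| Two-sided level | 77% v 87% | 67% v 77% |
|---|---|---|
| 0.05 | 80.1% | 66.9% |
| 0.05/2 | 71.3% | 56.1% |
| 0.05/3 | 65.8% | 50.0% |

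For example, at 0.05/3 and 77% v 87%: (0.10 − 2.394·0.03575)/0.03544 = 0.407, and Φ = 65.8%. Restoring 80% at that level would need 308 evaluable per arm (343 with dropout).

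**Step 3: all three strains, independent tests, by hand.**
- Bonferroni: 0.658 × 0.500 × 0.500 = 16.4%.
- No correction: 0.801 × 0.669 × 0.669 = 35.8%.
- Holm needs all three P ≤ 0.05, at least two ≤ 0.025 and at least one ≤ 0.05/3. The first two conditions give 0.7125·0.5608² + 0.0883·0.5608² + 2·0.7125·0.1079·0.5608 = 0.338, where 0.0883 = 0.8008 − 0.7125 and 0.1079 = 0.6687 − 0.5608. Subtracting the cases with none ≤ 0.05/3 (about 0.001) leaves 33.7%.

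**Step 4: correlated tests, by simulation.** 400,000 draws of three correlated normal test statistics, all strains improved by 10 points. Each cell is Bonferroni / Holm / no correction, in %.

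| Correlation of statistics | H1N1 | H3N2 or B | At least one | All three |
|---|---|---|---|---|
| 0 | 65.8 / 72.7 / 80.2 | 50 / 59 / 67 | 91.5 / 91.5 / 97.8 | 16.4 / 33.8 / 35.9 |
| 0.3 | 65.9 / 71.7 / 80.2 | 50 / 59 / 67 | 85.2 / 85.2 / 94.4 | 23.9 / 41.0 / 43.0 |
| 0.5 | 65.7 / 70.7 / 80.0 | 50 / 59 / 67 | 80.4 / 80.4 / 91.3 | 29.1 / 45.5 / 47.7 |
| 0.8 | 65.7 / 68.8 / 80.1 | 50 / 59 / 67 | 72.2 / 72.2 / 85.2 | 38.1 / 53.2 / 56.1 |

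In every draw Holm rejected everything that Bonferroni rejected. A second simulation generated patient-level binary outcomes with latent correlation 0 to 0.6. It gave all three strains in about 17-27% of trials with Bonferroni, 35-43% with Holm and 37-45% with no correction, and at least one strain in 92-84% under both corrections.

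**Step 5: checks on the limits.**
- Under the global null the familywise error is identical for the two procedures: 4.95% at correlation 0, 4.5% at 0.5 and 3.5% at 0.8.
- If only H1N1 benefits, H1N1 power is 65.8% with Bonferroni and 65.8-66.0% with Holm.
- Take 80% as the target for showing all three strains. At latent correlation 0 the Bonferroni shortfall is 80 − 17 = 63 points, and 80 − 37 = 43 of them remain with no correction at all, about two thirds.

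**The case against.** The strongest reply is that nothing here is wrong. Bonferroni controls the error rate, and preferring Holm is a choice between two valid methods. That stands, and the point is put as an improvement only.

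Second, the article does not fix a correction across strains. The wording leaves its use to judgement, defines no family, and sits beside a sample size at an unadjusted 5%. If one strain were primary, or if success required all three, no such correction would arise. The full protocol or analysis plan, not shown, may settle this. That also stands, so every power figure above is conditional on a correction being used across the strains.

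Third, a reader might infer that Bonferroni gives power away for nothing. The documents and figures do not support that. Bonferroni has simple simultaneous confidence intervals and Holm does not, and the chance of showing at least one strain is the same. The loss is small here because the article plans ordinary 95% intervals. An ordinary interval can, however, exclude no effect while the Holm-adjusted P-value exceeds 0.05, as can already happen beside a Bonferroni-adjusted one.

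Fourth, a reader might infer that a booster effective against all strains would be reported for only one because of the correction. That is not supported either. Holm also misses at least one strain in more than half of trials over latent correlation 0 to 0.6, and so does testing with no correction. The larger cause is sizing on the H1N1 rate alone, which leaves 67% power for H3N2 and B even at an unadjusted 5%.

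**Conclusion.** The point holds as an efficiency improvement. Wherever the plan would apply Bonferroni, Holm gives the same familywise error and at least as many rejections.

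Across the three strain-specific seroconversion tests, the gain is about 6 points of power for H1N1, about 9 for each of H3N2 and B, and roughly 16 to 18 for showing all three. These sizes rest on 231 per arm, an assumed 10-point benefit on every strain and a latent correlation of 0 to 0.6; only the first is in the article. The gain is nil for at-least-one-strain success and essentially nil if H1N1 alone benefits. It does not repair the unbudgeted cost of a correction or the lower power for the strains with a 67% control rate.

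It is a low-cost suggestion, not a defect that threatens the trial's conclusions.

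**What to change.** Under Statistical analysis, replace the Bonferroni clause with wording such as: the Holm step-down procedure, at a familywise two-sided 5%, will be applied across the three strain-specific seroconversion tests, and likewise to any other categorical comparisons where Bonferroni would have been used.

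Naming the three seroconversion tests matters as much as naming Holm. A bare swap of names would leave open whether and where a correction applies.

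Keep the planned ordinary 95% confidence intervals and label them as unadjusted beside the Holm-adjusted P-values. Do not extend the correction to titre comparisons, for which the article states none; that would add a penalty and work against the purpose of the change.

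The cost is one sentence, with no extra patients or data. The downside is the lack of simple matching simultaneous intervals. Because follow-up is complete, the change should be recorded and dated while the analysts are still blinded to treatment arm.

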**Methods/Design:**

This phase III, randomized, controlled, open-label clinical trial was conducted between October 2012 and December 2013 in 12 Spanish public referral hospitals. Solid organ transplant recipients (liver, kidney, heart or lung), older than 16 years of age more than 30 days after transplantation were eligible to participate. Patients (*N* = 514) were stratified 1:1 by center, type of organ and time after transplantation and who either received the standard single dose (*n* = 257) or were treated according to a novel influenza vaccination schedule comprising the administration of a booster dose 5 weeks after standard vaccination (*n* = 254). Seroconversion rates were measured as a determinant of protection against influenza (main outcome). Efficacy and safety outcomes were followed until 1 year after influenza vaccination with assessment of short-term (0, 5, 10 and 15 weeks) and long-term (12 months) results. Intention-to-treat, per-protocol and safety analyses will be performed.

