## Trial status

At the time this manuscript was submitted the TRANSGRIPE1-2 trial was closed. The recruitment period was closed in December 2012 with a total of 499 participants enrolled, and follow-up visits were completed in December 2013.

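### The sample size lets the 10% dropouts leave the analysis, but the ITT rule counts them as failures, so the stated 80% power does not apply to the stated analysis

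*Protocol article*

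**What the plan says.** The Sample size calculation section of the protocol article sets the target: "To achieve a 95% confidence level (significance level of 5%) and 80% statistical power to observe differences". It gives the rates: "we would expect to achieve 77% and 87% seroconversion rates in the control and experimental arms, respectively". It gives the loss allowance: "To estimate a 10% dropout rate per arm". From these it concludes that "the minimum number of patients was set at 231 units in each treatment arm, with a total of 462 evaluable participants to be recruited", and it then raises the total to 514 (257 per arm) to cover the losses.

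The Statistical analysis section defines the ITT set as consenting, randomised patients who had the first vaccine dose. It states that P-values "will be based on two-tailed tests", and it fixes the handling of missing outcomes: "The analysis will be performed on the ITT population, and missing data will be handled by imputing missingness to failure". A per-protocol analysis is also planned, which leaves out patients who discontinued.

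The Trial status section reports: "The recruitment period was closed in December 2012 with a total of 499 participants enrolled".

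**The concern.** The two sections treat the same lost patients in opposite ways. Dividing 231 by 0.9 assumes that the lost 10% drop out of the comparison and that the rates among those who remain are still 77% and 87%. The ITT rule keeps those patients in and scores each as a non-seroconverter. Both arms' rates fall, the difference between them shrinks in proportion, and the rates move towards 50%, where the binomial variance is larger. Enrolling 257 instead of 231 offsets only part of this.

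At stake is how a non-significant ITT result would be read. A reader of the article would take it as coming from a trial with a 20% chance of missing a 10-point benefit. Under the plan's own dropout figure that chance could be about 36% to 37%.

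**Working it through.** **Inputs** (Sample size calculation, Statistical analysis and Trial status): p1 = 0.77, p2 = 0.87; two-sided alpha 0.05 (z = 1.960); 80% power (z = 0.842); 1:1 allocation; 10% dropout per arm; 257 per arm planned; 499 enrolled, taken as 249.5 per arm.

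**Step 1: reproduce the plan's figures.** The pooled-variance formula for two proportions, with mean rate p̄ = 0.82, is

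n = [1.960 × √(2p̄(1−p̄)) + 0.842 × √(p1(1−p1) + p2(1−p2))]² / (p2−p1)²

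= (1.0649 + 0.4534)² / 0.10² = 230.5, so 231 per arm. Then 231 / 0.9 = 256.7, so 257 per arm and 514 in total. Both stated figures reproduce, and power at 231 evaluable per arm is 80.1%.

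**Step 2: apply the stated missing-data rule.** Let a fraction d of each arm's ITT set lack the primary titre, independently of response. Counted as failures, the analysed rates are 0.77(1−d) and 0.87(1−d), and the difference is 0.10(1−d). All n patients stay in the denominator. For d = 0.10:

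- rates 0.693 v 0.783; difference 0.090; mean 0.738
- standard error under the null at n = 257: √(2 × 0.738 × 0.262 / 257) = 0.03879
- standard error under the alternative: √((0.693 × 0.307 + 0.783 × 0.217) / 257) = 0.03859
- power = Φ[(0.090 − 1.960 × 0.03879) / 0.03859] = Φ(0.362) = 64.1%

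Exact binomial enumeration of the uncorrected χ² test gives 64.4%.

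**Step 3: vary the missingness.**

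| Missing per arm | Analysed rates | Power, 257 per arm | Power, 499 enrolled |
|---|---|---|---|
| 0% | 77.0% v 87.0% | 84.1% | 83.0% |
| 3% | 74.7% v 84.4% | 78.0% | 76.8% |
| 5% | 73.2% v 82.7% | 73.9% | 72.6% |
| 10% | 69.3% v 78.3% | 64.1% | 62.8% |

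Power crosses 80% at about 2.0% missing with 257 per arm, and at just over 1.4% with 499 enrolled.

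**Step 4: separate the causes.** If 10% of the 499 were left out of the analysis, 499 × 0.9 / 2 = 224.55 per arm would remain and power would be 79.0%. The fall from 79.0% to 62.8% is therefore due to the imputation rule, and recruiting 499 instead of 514 costs little. For scale, 80% power at 69.3% v 78.3% would take 374 per arm.

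**The case against.** The strongest reply is that 64% is one scenario and not a property of the trial. A reader might infer that the real power is 64%, but the article does not support that. It does not tie the 10% dropout to a time point. Follow-up lasts 12 months, whereas the primary objective in the Background is short-term immunogenicity, with visits at 5, 10 and 15 weeks. A patient lost after week 15 still has the short-term titres, and a patient lost before the first dose is outside the ITT set. The fraction missing the primary titre could therefore be well below 10%. This stands, and it is why the result must be given as a range. It does not remove the point: power is below 80% at 3% and at 5% missing too. The abstract also places long-term immunogenicity within the primary objective, which would bring later losses back in.

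The planned per-protocol analysis leaves out patients who discontinued. It matches the 231 evaluable per arm and would keep about 80% power. That is correct, but the sentence that fixes population and missing-data handling names the ITT set. Planned confidence intervals would help a reader judge a null result, but they do not correct the power statement.

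It could also be suggested that 77% and 87% already count missing patients as failures. The sample size section applies them to evaluable participants and then adds a separate loss allowance, so that reading does not fit.

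Three stronger readings should be set aside. The sample size arithmetic is not wrong: it reproduces exactly. Nothing here shows an inflated type I error, because with equal missingness unrelated to response the cost is attenuation of the difference and loss of power. The disagreement between participant counts is real, but it does not cause the power loss.

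**Conclusion.** Wrong as written. The 80% power belongs to an analysis of 231 evaluable patients per arm, not to the ITT missing = failure analysis that the article specifies. On the plan's own 10% the ITT power is about 64% at 257 per arm and about 63% with 499 enrolled. Over 3% to 10% missing it runs from about 78% down to 64% at 257 per arm, and from about 77% down to 63% with 499 enrolled.

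These figures assume the planned 77% and 87% among patients with titres, missingness that is equal between arms and unrelated to response, an uncorrected χ² test, and, for the 10% case, that every dropout received the first dose and lacks the primary titre.

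**What to change.** Keep the 231/257 calculation in the Sample size calculation section as the a priori record, and label it as the power for evaluable patients. Add beside it a statement such as: with missing outcomes counted as failures in the ITT set, power is about 64% at 257 per arm (63% with 499 enrolled) if 10% lack the primary titre, about 74% (73%) at 5% and about 78% (77%) at 3%. Say which visit these percentages refer to.

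Leave the stated ITT analysis as it is. Any complete-case or multiple-imputation analysis should be added only as a sensitivity analysis, fixed before unblinding. The 79.0% above is a complete-case figure; no power has been computed for multiple imputation.

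As a separate reporting correction, reconcile the abstract's N = 514 and arms of 257 and 254 (257 + 254 = 511) with the 499 enrolled, and say which numbers are planned and which were randomised and vaccinated.

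The cost is wording only: no new patients and no change to the main analysis, but a less favourable power statement. An added sensitivity analysis would cost a small amount of analysis work.
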